### Replacing withdrawn participants

For each dosing protocol (single dosing and multiple dosing), a minimum of four participants (randomly selected) will be on stand-by – to replace any subject withdrawals or non-attendances. The stand-by subjects will have undergone screening and written consent and will be asked to be available during the day before and the day of dosing and will be reimbursed for lost wages accordingly. Subjects that complete dosing and monitoring at the inpatient facility, but who do not attend out-patient follow-up (Day 2, 5 and 42) will not be replaced.

## Storage, packaging, dispensing, and administration of the investigational medicinal product

### Storage

The capsules and solution for injection will be stored in a pharmacy with temperature regulation as this should not exceed 25 °C. The capsules will be kept dry as per recommendations on summary of product characteristics. The shelf-life for the commercially available pharmaceutical preparation Dimaval
^
^®^
^ is 3 years for the capsules and the ampoules. The expiry date is stated on each package.

### Packaging and labelling

Packaging and labelling of the investigational medical product will comply with the Kenya Pharmacy and Poisons Board (PPB) labelling requirements, as per their guidelines for the conduct of clinical trials in Kenya.

### Dispensing procedures

The study drug will be stored in the pharmacy at KCH according to the manufacturer’s specifications. The drug, dose and subject identity will be confirmed by one pharmacist or pharmacy technician and one study team member.

### Dose administration

Oral unithiol will be administered with 240mL of water and will be swallowed as whole tablet(s). Food will not be consumed for at least one-hour after dosing, as per product literature.

Intravenous dosing will be infused over a minimum period of 5 minutes, as per a previous study
^
27
^, with the subject lying flat with blood pressure monitoring during the infusion, at 5 minutes and at 15 minutes (more frequent monitoring will be provided if the responsible clinician identifies a clinical need). The solution for infusion will be prepared according to the product literature.

### Treatment compliance

All doses of the IMP will be administered under direct observation by a trained study team member. Participants can withdraw from the study if they no longer wish to receive the medication.

### Overdosage

Overdose of unithiol will be prevented as subjects will not have access to the medication, except for the individual doses they are to receive. The IMP will be stored securely in a locked drug cabinet. Doses will be confirmed by two study team members before administration.

In the rare event of overdose, participants will be managed with necessary supportive measures (including intravenous fluids) and the PI, in discussion with clinical investigators, hospital staff and the DSMB will decide whether transfer to a facility with intensive care and dialysis/haemofiltration facilities is necessary.

### Rescue medication

There is no antidote to unithiol. Dialysis does remove the drug.

## Assessment of pharmacokinetics and pharmacodynamics

### Pharmacokinetics

The secondary outcome is to define the pharmacokinetic profile of unithiol. Although most of the pharmacokinetic analysis will be completed after all the subjects have completed follow-up in the trial, preliminary pharmacokinetic data will be made available prior to commencing the multiple dosing stage of the trial. The purpose of this preliminary data will be to predict a dose and dosing interval that will provide consistent plasma drug levels and not pose a risk of accumulation of the study drug following multiple dosing. Multiple dosing will only proceed once the DSMB have reviewed adequate pharmacokinetic data from the single dosing stage to be satisfied that the proposed dosing regimen will not lead to accumulation of the study drug.

This will be undertaken in collaboration with the University of Liverpool. Samples will be shipped to the Liverpool Bioanalytical Facility (GCP Laboratories, [name]) for the purposes of measuring drug concentrations. This is necessary to fulfil regulatory requirements for pharmacokinetic analysis. Drug concentrations will be quantified by validated liquid chromatography-mass spectrometry.

### Pharmacodynamics

An exploratory outcome is to assess the efficacy of unithiol to inhibit the pathogenic actions of venom,
*ex vivo*. If the pharmacodynamic assay produces results that are deemed reliable, then pharmacodynamic data from the single dosing stage could be used to guide the dosing regimen for the multiple dosing stage. If the pharmacodynamic assay does not produce useful results, then dose and dosing frequency decisions will be made based on safety and preliminary pharmacokinetic data.

*Ex vivo* assays will be developed for the purposes of establishing a dose-response and estimating a pharmacodynamic profile. These assays will rely on spiking subjects’ plasma with venom
*ex vivo* and measuring activity of snake venom metalloproteinases. These assays are being developed for the purposes of this study, and a published validated assay does not exist. It would not be appropriate to assign these assays as primary outcome variables as they are experimental and represent an indirect estimate of efficacy.

These assays will continue to be refined during this study. They primarily represent a tool to compare venom metalloproteinase inhibition between subjects receiving different doses of unithiol, rather than a direct measure of efficacy. Where possible, these assays will be conducted and refined in the laboratory facilities at KEMRI-CGMRC. Split samples will also be shipped to Liverpool School of Tropical Medicine Centre for Snakebite Research & Interventions (LSTM CSRI).

## Study governance: local safety monitor and data safety monitoring board

### Local safety monitor

•      The local safety monitor (LSM) will be a clinician resident in Kilifi (therefore likely to be linked to or a staff member of KWTRP) but independent of the study team. The LSM will act as a semi-independent assessor of participants experiencing important safety events at the request of the DSMB and will provide their observations to the DSMB and/or local clinicians or study team members where appropriate.

### Data and safety monitoring board

•      The DSMB will include a minimum of 3 members with at least 1 clinician with expertise of the local context and 1 statistician.

•      The DSMB charter has been uploaded the
Harvard Dataverse
^
41
^

•      At least one of the following investigators will attend DSMB meetings: [name], [name] or [name] (either remotely or in-person). The DSMB will have access to all relevant data on administration of unithiol. The independent local clinician will have expert knowledge of the Kenyan context. The DSMB will be convened at the start of the study before unithiol is administered, to review the protocol and their responsibilities. Planned DSMB meeting will occur before every dose escalation, although the DSMB can hold additional
*ad-hoc* meetings if they deem it necessary. A local safety monitor (LSM) will also be appointed prior to this to provide independent safety assessments of participants. The DSMB will review:

•      all SAEs/SUSARs (serious adverse events/suspected unexpected serious adverse reactions)

•      SAEs will be reviewed alongside an updated summary of all severe adverse events reported to that date.

•      Clinically relevant signs or symptoms or intolerable adverse events of similar nature occurring in 2 or more subjects in a group

•      Summaries of all adverse events will be reported to the sponsor and DSMB. However, investigators or the local safety monitor can request the DSMB to review any non-serious non-severe adverse events that raise concern. The Investigators will be responsible for reporting a summary of safety data to the Scientific and Ethics Review Unit (SERU) and PBB, as per their guidelines.

## Assessment of safety

### Adverse events (AEs)

Both solicited and unsolicited AEs will be recorded on the participant’s CRF until the end of the 6-month follow-up period. The diagnosis, date and time of onset, outcome, severity, and relationship to unithiol administration will be established. Details of any treatment or concomitant interventions will be recorded.

If any pregnancies occur with 2 months of receiving unithiol, the participant will be referred for appropriate antenatal care. Unithiol has a short half-life and, as participants will undergo pregnancy testing, it is very unlikely that any pregnancies will occur whilst unithiol is detectable in the circulation. Nevertheless, if this were to occur during the trial the pregnant participant would be followed-up until term and (as a minimum) their baby would be examined by a paediatrician at 6-weeks following birth. Any congenital anomaly or birth defect would be reported as a serious adverse event.

During the in-patient admission, the study clinician will evaluate for solicited adverse events. Solicited AEs will also be elicited at every follow-up visit (day 2, day 5, day 42 and 6 months). Assessing the severity of adverse events will be the responsibility of a clinical or medical officer.

### Solicited adverse events

Solicited adverse events are those that have been associated with unithiol and are listed in the summary of product characteristics. These are summarised in
Table 4.

**Table 4. T4:** Solicited adverse events.

Category	Solicited adverse events
Symptoms	Nausea, weakness, loss of appetite, dysgeusia (change in taste), painful injection site, abdominal pain
Physical observations	Shivering, fever, skin reactions (itching rash), Stevens-Johnson’s syndrome, hypotension (with intravenous unithiol)
Laboratory abnormalities	Leucopaenia, transaminitis, kidney injury (raised urea and creatinine)

### Definitions and monitoring of AEs

The definitions of adverse events (AE), adverse reactions (AR), serious adverse events (SAE), serious adverse reactions (SAR), and suspected unexpected serious adverse reactions (SUSAR) are available in
Table 5.

**Table 5. T5:** Definitions of adverse events.

Term	Definition
Adverse Event (AE)	Any untoward medical occurrence in a patient or clinical investigation subject occurring in any phase of the clinical study whether or not considered related to the study drug. This includes an exacerbation of pre-existing conditions or events, intercurrent illnesses, or drug interactions. Anticipated day-to-day fluctuations of pre-existing conditions, that do not represent a clinically significant exacerbation, will not be considered AEs. Discrete episodes of chronic conditions occurring during a study period will be reported as adverse events to assess changes in frequency or severity. Unsolicited adverse events will be documented in terms of a medical diagnosis(es). When this is not possible, the AE will be documented in terms of signs and symptoms observed by the investigator or reported by the subject. Pre-existing conditions or signs and/or symptoms (including any which are not recognized at study entry but are recognized during the study period) present in a subject prior to the start of the study will be recorded on the Medical History form within the subject's case report form (CRF).
Adverse Reaction (AR)	An untoward and unintended response in a participant to an investigational medicinal product which is related to any dose administered to that participant. The phrase "response to an investigational medicinal product" means that a causal relationship between a trial medication and an AE is at least a reasonable possibility, i.e., the relationship cannot be ruled out. All cases judged by either the reporting medically qualified professional or the Sponsor as having a reasonable suspected causal relationship to the trial medication qualify as adverse reactions. It is important to note that this is entirely separate to the known side effects listed in the SmPC. It is specifically a temporal relationship between taking the drug, the half-life, and the time of the event or any valid alternative aetiology that would explain the event.
Serious Adverse Event (SAE)	A serious adverse event is any untoward medical occurrence that: • results in death • is life-threatening • requires inpatient hospitalisation or prolongation of existing hospitalisation • results in persistent or significant disability/incapacity • consists of a congenital anomaly or birth defect Other ‘important medical events’ may also be considered serious if they jeopardise the participant or require an intervention to prevent one of the above consequences. NOTE: The term "life-threatening" in the definition of "serious" refers to an event in which the participant was at risk of death at the time of the event; it does not refer to an event which hypothetically might have caused death if it were more severe. “Hospitalisation” signifies that the subject has been detained (usually involving an overnight stay) at a hospital for observation and/or treatment above that routinely offered at the inpatient trial facility. When in doubt as to whether hospitalisation occurred or was necessary, the adverse event will be considered as serious. Hospitalisation for elective surgery or routine clinical procedures, which are not the result of an adverse event, will not be considered adverse events and should be recorded on a clinical assessment form and added to the CRF.
Serious Adverse Reaction (SAR)	An adverse event that is both serious and, in the opinion of the reporting Investigator, believed with reasonable probability to be due to one of the trial treatments, based on the information provided.
Suspected Unexpected Serious Adverse Reaction (SUSAR)	An adverse reaction, the nature or severity of which is not anticipated based on the applicable product information is considered as an unexpected adverse drug reaction. Where the adverse reaction is also considered to have a possible, probable, or definite relationship with the drugs given, and also meets the criteria for a serious adverse reaction, it is termed a Suspected Unexpected Serious Adverse Reaction (SUSAR). These events are subject to expedited reporting as for SAEs.

To avoid confusion or misunderstanding of the difference between the terms ‘serious’ and ‘severe,’ the following note of clarification is provided: ‘severe’ is often used to describe intensity of a specific event, which may be of relatively minor medical significance. ‘Seriousness’ is the regulatory definition supplied above. Detailed guidance can be found here:
http://ec.europa.eu/health/files/eudralex/vol-10/2011_c172_01/2011_c172_01_en.pdf

### Assessing the relationship between an adverse event and the investigational medicinal product

The causal relationship between an adverse event and the study drug is defined in
Table 6.

**Table 6. T6:** Categorizing a causal relationship.

Category		Definition
0	No Relationship	No temporal relationship to study product ** *and* ** Alternate aetiology (clinical state, environmental or other interventions); ** *and* ** Does not follow known pattern of response to study product
1	Unlikely	Unlikely temporal relationship to study product ** *and* ** Alternate aetiology likely (clinical state, environmental or other interventions) ** *and* ** Does not follow known typical or plausible pattern of response to study product.
2	Possible	Reasonable temporal relationship to study product; ** *or* ** Event not readily produced by clinical state, environmental or other interventions; ** *or* ** Similar pattern of response to this form of therapeutic
3	Probable	Reasonable temporal relationship to study product; ** *and* ** Event not readily produced by clinical state, environment, or other interventions ** *or* ** Known pattern of response seen with study product
4	Definite	Reasonable temporal relationship to study product; ** *and* ** Event not readily produced by clinical state, environment, or other interventions; ** *and* ** Known pattern of response seen with study product

### Severity grading of adverse events

All adverse events will be severity graded using the definition shown in
Table 7. Severity grading of abnormal vital signs will be categorised as shown in
Table 8.

**Table 7. T7:** Severity grading of adverse events.

Grade	Definition
0	None
1	Mild: Transient or mild discomfort (< 48 hours); no medical intervention/therapy required
2	Moderate: Mild to moderate limitation in activity - some assistance may be needed; no or minimal medical intervention/therapy required
3	Severe: Marked limitation in activity, some assistance usually required; medical intervention/therapy required, hospitalization possible

**Table 8. T8:** Severity grading of abnormal vital signs.

Parameter	Grade 1 (mild)	Grade 2 (moderate)	Grade 3 (severe)
Fever	37.6°C - 38.0°C	38.1°C – 39.0°C	>39.0°C
Tachycardia (bpm) *	101 – 115	116 – 130	>130
Bradycardia (bpm) **	50 – 54	40 – 49	<40
Systolic hypertension (mmHg)	141 – 159	160 – 179	≥180
Diastolic hypertension (mmHg)	91 – 99	100 – 109	≥110
Systolic hypotension (mmHg) ***	85 – 89	80 – 84	<80

*Taken after ≥10 minutes at rest **When resting heart rate is between 60 – 100 beats per minute. Use clinical judgement when characterising bradycardia among some healthy subject populations, for example, conditioned athletes. ***Use clinical judgement, particularly in subjects with low body weight. Consider checking lying and standing blood pressure to test for a postural drop of >20 mmHg if safe to do so. Do not record as an adverse event if hypotension is asymptomatic (e.g., absence of light-headed feeling)

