### Cardiovascular effects

Rapid infusion of unithiol solution via the intravenous route has been associated with transient asymptomatic hypotension in a single published article. In a previous pharmacokinetic study of unithiol, two of five participants developed transient falls in systolic blood pressure, of 20 mmHg
^
27
^. These episodes were not associated with any symptoms, any change in heart rate, or any fall in diastolic blood pressure. Unithiol is not cardiotoxic and is not associated with any cases of clinically significant cardiac arrhythmia.

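### The known intravenous effect, a symptom-free 20 mmHg systolic fall, cannot become a recorded adverse event under Table 8 and its footnote, and no planned DSMB summary named in the article shows it

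*Protocol article*

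**What the plan says.** All of the following is in the protocol article.

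- **Cardiovascular effects.** Rapid intravenous infusion "has been associated with transient asymptomatic hypotension in a single published article". The size is given as a change: "two of five participants developed transient falls in systolic blood pressure, of 20 mmHg". The section adds: "These episodes were not associated with any symptoms, any change in heart rate, or any fall in diastolic blood pressure".
- **Solicited adverse events, Table 4.** The physical observations include "hypotension (with intravenous unithiol").
- **Dose administration.** Intravenous doses are given "with the subject lying flat with blood pressure monitoring during the infusion, at 5 minutes and at 15 minutes".
- **Severity grading of adverse events.** All adverse events are graded on the symptom and function scale of Table 7. In addition: "Severity grading of abnormal vital signs will be categorised as shown in" Table 8. The row "Systolic hypotension (mmHg") has grade 1 at 85–89, grade 2 at 80–84 and grade 3 below 80. Its footnote allows clinical judgement, suggests an optional lying and standing check for a postural drop of more than 20 mmHg, and ends: "Do not record as an adverse event if hypotension is asymptomatic (e.g., absence of light-headed feeling").
- **Dose.** The DSMB's decisions to repeat, reduce or space out dose levels rest on adverse event data.
- **Justification for the proposed dose.** The DSMB sets the CIV2 dose from emerging data. It is expected to be 5 mg/kg and may go up to 10 mg/kg; CIV1 receives 3 mg/kg.
- **Safety analyses.** Before each escalation the DSMB receives adverse event frequency, grade and relationship. Changes in ALT, creatinine, haemoglobin, white cell count and platelet count are shown at every safety review. Blood pressure is not on that list.

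**The concern.** The article describes the expected effect as a change within a person, but grades it as a level. It also describes the effect as symptom-free, while its recording rule omits symptom-free cases. Hypotension is solicited because of this effect, yet the recording and grading rules do not capture the form in which it was observed.

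At stake is what the trial can say about intravenous tolerability. Sixteen people receive intravenous drug (two cohorts of 8). If CIV1 reproduced the published finding exactly, the adverse event tables could show no hypotension at all. Those tables and five laboratory changes are what the article commits to put before the DSMB. The readings are planned, but no summary named in the article uses them.

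**Working it through.** The article states no figure on this point, so there is none to reproduce.

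**Inputs from the article.** Table 8 cut-offs: 89 mmHg or lower (grade 1), 84 or lower (grade 2), below 80 (grade 3). Fall: 20 mmHg. Frequency: 2 of 5. Intravenous cohorts: 2 of 8 people each.

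**Input assumed.** The article gives no baseline systolic distribution. I take it as normal with mean 110 to 130 and SD 10 to 15 mmHg.

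**Step 1: the rules as written.** Take a symptom-free fall from 120 to 100 mmHg. If it counts as hypotension, as the Cardiovascular effects section uses the word, the footnote excludes it from recording. If it does not count because 100 is above 89, Table 8 has no grade for it. Table 7 does not help, because its grades depend on discomfort, limited activity or intervention. The expected number of recorded events is therefore 0, whatever the true rate of such falls.

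**Step 2: the cut-offs alone, with the footnote set aside.** A 20 mmHg fall reaches grade 1 only if baseline − 20 ≤ 89, so baseline ≤ 109. Grade 2 needs baseline ≤ 104 and grade 3 needs baseline < 100. The fall needed to reach 89 is 110 − 89 = 21, 120 − 89 = 31 or 130 − 89 = 41 mmHg. From 120, grade 3 needs a fall of 120 − 79 = 41 mmHg.

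**Step 3: share of 20 mmHg falls left ungraded.** Share = 1 − Φ((109.5 − mean)/SD), using 109.5 because readings are whole numbers. For mean 120 and SD 12: 1 − Φ(−0.875) = 1 − 0.191 = 0.81.

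| Baseline mean | SD 10 | SD 12 | SD 15 |
|---|---|---|---|
| 110 | 52% | 52% | 51% |
| 115 | 71% | 68% | 64% |
| 120 | 85% | 81% | 76% |
| 125 | 94% | 90% | 85% |
| 130 | 98% | 96% | 91% |

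The range is 51% to 98%. Counting only people whose baseline is at least 90 mmHg, so not already in a Table 8 grade, changes it to 53% to 98%.

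**Step 4: people per intravenous cohort.** At the published rate, 8 × 2/5 = 3.2 of 8 would have the fall. The exact 95% interval for 2 of 5 is 5% to 85%, or about 8 × 0.05 = 0.4 to 8 × 0.85 = 6.8 of 8. With the footnote set aside, and at mean 120 and SD 12, 3.2 × 0.19 = 0.6 of 8 would reach grade 1. With the footnote in force and the falls symptom-free, the number recorded is 0.

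**Step 5: does other text close the gap?** The postural check is optional, carries no grade, and compares lying with standing. The monitoring at dosing is done lying flat, and the comparison of interest is post-dose against pre-dose. The Safety analyses section names no blood pressure summary.

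**The case against.** The strongest reply is that Table 8 is not itself wrong. A conventional level-based scale can stand, and a change-from-baseline table is the kind of detail that the separate SAP or DSMB charter may hold. Neither is shown here. The Study governance section gives the DSMB access to all relevant dosing data, and investigators or the local safety monitor can refer any event that worries them. The Safety analyses list does not say that nothing else will be presented. The published effect was transient and symptom-free, and the holding criteria concern clinically relevant, intolerable, severe or serious events, so a tabulated fall need not trigger any of them.

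Much of this stands. It limits the consequence and means Table 8 can stay. It does not remove the conflict between the described effect, the solicited event and the footnote, which lies within the article. Access to raw readings also does not ensure that anyone tabulates them.

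Three stronger readings are tempting, and the documents do not support them.

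- A reader might infer that no fall from 120 to 100 mmHg can ever be graded. A person who feels light-headed at 100 mmHg can be graded under Table 7. The gap concerns symptom-free falls.
- A reader might infer that the effect will grow from CIV1 to CIV2. The article links it to rapid infusion in one study at one dose, 3 mg/kg, and gives no dose–response for blood pressure.
- A reader might infer that the DSMB's view of intravenous tolerability will be too favourable. The documents show only that the planned summaries could omit the effect.

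**Conclusion.** The point holds for symptom-free falls. Under the rules as written, a symptom-free 20 mmHg systolic fall yields no recorded adverse event, and this needs no assumption about baseline pressure. The cut-offs are a second, independent obstacle: with the footnote removed, 51% to 98% of such falls would still be ungraded. That range rests on the assumed normal baselines; at its low end only about half are missed. How many people would be affected is very uncertain, since the 40% rate comes from five volunteers.

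The consequence is a possible gap in the planned safety summaries before the CIV2 dose is decided and in the final statement on intravenous tolerability. It should be corrected because the remedy is small and the readings are already planned.

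**What to change.** Keep Table 8 for grading. In the Safety analyses section, add for CIV1 and CIV2 the maximum systolic fall from the participant's own pre-infusion reading, whether or not symptoms occurred. Give the median and range per cohort, and the number with a fall of 20 mmHg or more. That figure is the one in the article's Cardiovascular effects section and serves only as a reporting count, not a new grade or clinical rule. Report the CIV1 results to the DSMB before the CIV2 dose is decided, and both cohorts in the final safety analysis.

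The Cardiovascular effects section, the Table 4 entry for intravenous hypotension and the Table 8 footnote must also be reconciled. How the event is defined clinically is for the investigators to settle.

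Cost: one derived variable, one table row, and a pre-infusion reading recorded as baseline. The later readings are already required under Dose administration.
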